## End of the Trial

The trial will end when the last participant has completed the final follow up (and qualitative interview, if they also consent). We will then complete the Declaration of the End of Trial and submit to the HRA REC. We will notify the REC of the end of the trial within 90 days of completion or within 15 days, if the study should end prematurely. Following this, the process for closing the trial at the sites be undertaken. A summary report will be provided to the REC within 12 months of the end of trial.

## INTERVENTION

**iMAPS.** Therapists delivering the iMAPS therapy approach (Taylor et al. 2019) will be trained and supervised by lead \applicant and co-applicant experts in psychological therapy for psychosis to deliver the expanded 12 sessions of individualised, personalised iMAPS intervention over a twelve-week therapy phase. Please see our published iMAPS treatment approach journal publication for more details (Taylor et al 2019).

The therapy includes novel change techniques including imagery re-scripting (imaging an image or memory and changing the ending to change the meaning) of past events, imagery re-scripting of flash-forwards, working with nightmares and creating positive imagery. Other techniques used to work with negative core beliefs and images are i) learning that pushing images away makes them come back stronger (image suppression and responding differently), ii) testing beliefs about images and schemas (behavioural experiments), iii) changing (manipulation) of images and iv) working with upsetting memories. The use of the “Safe Place” image, as the first introduction to imagery work, ensures that patients have a personalised strategy to reduce any distress experienced. There are clear distress protocols developed and agreed in advance with patients (including managing dissociation) before the imagery sessions begin (after a careful assessment and formulation).

Please see more details in Table 1.**Table 1** Outline of the iMAPS Therapy (Taylor et al 2019)

Training and Supervision by CT, JK with support from KB, AA

Table 1. *iMAgery focused therapy for PSychosis (iMAPS)*

| Phase of Treatment | Main approach |
| --- | --- |
| Assessment, Goals, Psychoeducation | Interview  Imagery measures – Visual Analogue Scale, Spontaneous Use of imagery Scale (SUIS), Image Diaries, Assessing different types of imagery, Assessment of schema – core schema, early negative schema, schema modes |
| Formulation & Case Conceptualisation | Shared psychological formulation |
| Intervention |  |
| Imagery CT Approaches  Safe Place Image | A real or imaged safe place, described in detail, across each of the senses that gives a strong sense of safety and happiness |
| Image Suppression &  Behavioural Experiments | Similar to thought suppression experiments and behavioural experiments within other areas of CBT but with a focus on images |
| Manipulation of Images | To show images are only a mental event – improve sense of control  Test any beliefs or appraisals regarding an image meaning you are “going mad” |
| Working with upsetting memories | Transformation  Provide a wider context by running image on past the worst point  Updating aspects of the image  Emotional bridge to past (also use as diagnostic imagery exercise – can identify key life events which link to core beliefs, current images and psychotic symptoms). |
| Imagery Rescripting Approaches  Imagery Rescripting past events  Imagery Rescripting Flash-forwards | Past events  Future Flash-forwards  Discussion of negative beliefs re self and others, schemas – Imagery rescripting to change future anticipated image |
| Working with night-time imagery | Updating aspects of the image, rescripting new endings |
| Creating Positive Imagery | Deliberately generating positive images of the future |

We will follow best practice guidelines in delivering iMAPS, however, video therapy (Telehealth) is becoming part of routine care. The feasibility of the intervention will be assessed by the number of sessions attended, cancelled and drop-out rates. Intervention fidelity will be assessed by a random selection of tapes being rated using an iMAPS therapy checklist. In addition, therapists will complete a standardised session record form to monitor session content, in terms of therapy milestones and strategies permitted within the therapy protocol.

The feasibility of the intervention will be assessed by the number of sessions attended, cancelled and drop-out rates. Intervention fidelity will be assessed by a random selection of video tapes being rated using an iMAPS therapy checklist. In addition, therapists will complete a standardised session record form to monitor session content, in terms of therapy milestones and strategies permitted within the therapy protocol. Therapists will also complete a “therapy session record”, which will briefly document the main focus and techniques used from the iMAPS protocol. Therapists will also assess images each session, and record imagery characteristics for the main images. Similar to iMAPS (Taylor et al. 2020) where participants were offered the opportunity to have a CD copy of a therapy session, where the therapist is happy to and the participant is happy to, we will offer this opportunity to participants to also record the therapy session on their mobile phone/smartphone, so they can listen back to it in-between sessions to help consolidate learning. This is recommended in several CBT protocols but not widely undertaken in routine practice in several services.

**Usual Care**

Usual care will involve interventions offered by an early intervention service or a community mental health team (fortnightly/monthly visits from social worker, mental health nurse, outpatient psychiatry reviews quarterly, medication, routine CBT). The study would not seek to restrict access in routine care to CBT. We will record during the trial by asking participants and by reviewing their clinical record and record any service users in the usual care arm of the trial who receive routine CBT or other psychological intervention. However, we know there are still significant barriers to NHS therapy. The 2020 English NCAP Psychosis National Audit collected data on access to CBT, defining a course of CBT as receiving just one session of therapy, (rather than the min. 16 sessions recommended by NICE). Even with this low threshold, only 49% of service users had this offer in EI. Secondary care services have historically had even poorer commissioner investment.

**ANCILLARY AND POST-TRIAL CARE**

The iMAPS therapy is designed to be a stand-alone psychological therapy. Participants who wish to access further psychological assessment and therapy will be signposted to accessing this via the local NHS clinical services which they are eligible to be referred to.

## ADVERSE EVENTS

***Definitions***

| **Term** | **Definition** |
| --- | --- |
| **Adverse Event (AE)** | Any untoward medical occurrence in a participant to whom psychological therapy/assessment or qualitative interview has been administered.  Non severe adverse events will be defined as a score of >3 (Agree quite a lot or a lot) on any item of the participant rated 26 item Adverse Events of Psychotherapy Questionnaire (AEP; Hutton, 2016; Pyle et al 2016) which is given to participants on either completion of therapy, or if they have given informed consent, sent to those who drop out or end therapy early. |
| **Adverse Reaction (AR)** | An untoward and unintended response in a participant to a psychological therapy/assessment or qualitative interview which is related to the therapy/assessment or interview administered to that participant.  The phrase "response to a psychological therapy/assessment or qualitative interview" means that a causal relationship between a trial therapy/assessment or interview and an AE is at least a reasonable possibility, i.e. the relationship cannot be ruled out.  All cases judged by either the reporting clinically qualified professional or the Chief Investigator (acting on behalf of the Sponsor) as having a reasonable suspected causal relationship to the psychological therapy/assessment or qualitative interview qualify as adverse reactions. |
| **Serious Adverse Event (SAE)** | A serious adverse event is any untoward medical occurrence that:   - results in death - is life-threatening - requires inpatient hospitalisation or prolongation of existing hospitalisation - results in persistent or significant disability/incapacity - consists of a congenital anomaly or birth defect   Other ‘important medical events’ may also be considered serious if they jeopardise the participant or require an intervention to prevent one of the above consequences.  NOTE: The term "life-threatening" in the definition of "serious" refers to an event in which the participant was at risk of death at the time of the event; it does not refer to an event which hypothetically might have caused death if it were more severe.  In line with an approach previously used (Pyle et al 2016) which was adapted from Klingberg et al 2012), in addition we will define serious adverse events as:   1. death by suicide 2. suicide attempt 3. suicidal crisis without attempt (rating 2 on item 8 of Calgary Depression Rating Scale for Schizophrenia CDSS) 4. severe symptoms increase (rating of > 6 on the patient or researcher rated CGI and CGI-I). |
| **Serious Adverse Reaction (SAR)** | An adverse event that is both serious and, in the opinion of the reporting Investigator, believed with reasonable probability to be due to the psychological therapy/assessment or qualitative interview, based on the information provided. |
| **Related and Unexpected Serious Adverse Reaction** | A serious adverse reaction, the nature or severity of which is not consistent with the effects or consequences of a psychological intervention. |

NB: to avoid confusion or misunderstanding of the difference between the terms “serious” and “severe”, the following note of clarification is provided: “Severe” is often used to describe intensity of a specific event, which may be of relatively minor clinical significance. “Seriousness” is the regulatory definition supplied above.

Our iMAgery focused therapy for Psychosis approach has previously been tested in a case series and no severe adverse events were reported. Building on work by others in psychological treatments for psychosis, we wish to carefully record and report adverse events of psychological interventions and wish to implement a protocol developed assessing and managing any such risk, which will be completed at end of treatment and at follow up by research assistants who are blind to the allocated group. We are adding the use of the CGI and additional criteria below.

This protocol will also be completed by clinicians during the intervention, that is each session, to complete an assessment of severe adverse events, for clinical purposes.

## Operational definitions for (S)AEs

**AEs**

All adverse events **related** to the psychological therapy/assessment or qualitative interview that occur between baseline and end of study will be recorded in the participant medical notes and in the appropriate section of the trial CRF.

**AEs that do not require reporting**

Any untoward medical occurrence that is **not** related to the psychological therapy/assessment or qualitative interview that has been administered.

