### Participant withdrawal

Participants in the study are free to withdraw from participating at any point, without giving a reason and without their legal rights or usual care being impacted. It is possible for a participant to with draw from receiving the therapy, but continue to remain in the trial for the follow up assessments, in essence, participants will be asked if they are willing to continue data collection assessments at 16 weeks and 28 weeks, if they wish to withdraw from the iMAPS intervention. While being reminded of their right to withdraw without giving a reason, we will politely ask if they are willing to give a reason, but remind them that this is entirely voluntary.

If continued participation for some reason is assessed by the researchers to be harmful in some way, then we may withdraw a participant. The Trial Steering Committee (TSC) which incorporates a Data Monitoring and Ethics function will review all instances of adverse events, regardless of whether they are judged to be attributable to the trial or interventions. Reviewing this information, the independent committee members will decide if a participant should be withdrawn from the study. All adverse events deemed related to study participation will be reported the Research Ethics Committee (See Section 9 for further details).

There is a possibility that individuals taking part may lose capacity to consent to continue participating in the study. In this event, we would pause their participation to see if they regain their capacity (acknowledging that capacity fluctuates in people with psychosis and may be temporary). However, if they continue to lack capacity, this may also mean they are no longer able to consent to ongoing participation in the study or for their data to be retained. In line with previous studies (including the iMAPS case series) we will seek informed consent in advance from all participants to retain their data if they subsequently withdraw because of loss of contact or are withdrawn by the study team due to loss of capacity

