**SAEs**

All SAEs **related** to the psychological therapy/assessment or qualitative interview occurring between baseline until end of study must be recorded on the SAE report form and emailed to Sponsor immediately and within 24 hours of the research staff becoming aware of the event. Refer to the SAE form for the information that will be collected for all SAEs.

Any change of condition or other follow-up information should be emailed to the Sponsor as soon as it is available or at least within 24 hours of the information becoming available. Events will be followed up until the event has resolved or a final outcome has been reached.

| **Email completed all SAEs FAO:**  [**[contact]**](mailto:[contact])  [**[contact]**](mailto:[contact]) |
| --- |

SAEs must be followed-up until resolution and sites must provide follow-up SAE reports if the SAE had not resolved at the time the initial report was submitted.

On receipt of the SAE Report Form, the Sponsor will send an acknowledgement of the SAE. This acknowledgement will include an SAE reference number which should be included on all future correspondence regarding the SAE.

The SAE Report Form will be reviewed by the CI for assessment of causality. If the SAE is related to the psychological therapy/assessment or qualitative interview, the CI will review the expectedness in relation to the nature or severity of an event which is not consistent with the effects or consequences of a psychological intervention. In the case that the SAE is related and **unexpected**, the study team will submit a report to REC, HRA and the Sponsor within the expedited timeframes.

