### Guidelines for stopping the trial early

There are no statistical reasons specified for stopping the trial early. The Chair of the TSC reviewed all serious adverse events. The trial would be stopped early to prevent harm, if there were an undue number of related SAE. The TSC also considered any relevant safety data, any recommendations for early closure of the study on this basis would had been based on their expert opinion, there were no formal statistical criteria specified for stopping the trial early.

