## Harms

The number of safety events (e.g., AEs and SAEs) and number (and proportion) of participants reporting at least one safety event will be summarised by treatment arm. Summary measures will be number (%).

Safety events will also be tabulated by:

- Death by suicide
- Suicide attempt
- Suicidal crisis without attempt (rating 2 on item 8 of Calgary Depression Rating Scale for Schizophrenia CDSS)
- Severe symptoms increase (rating of > 6 on the patient or researcher rated CGI and CGI-I)

They will be reported by both overall and by treatment arm.

Treatment effects will be estimated by the difference in event rates and 95% CI for the differences.

In addition, we will tabulate and present frequencies of the endorsed individual items in the Adverse Effects in Psychotherapy (AEP) scale (29) for those participants allocated to the intervention arm. This is a self-report measure of potential adverse effects completed by the participants at the end of therapy assessment measuring 7 broad categories: worsening difficulties, poor engagement (including low motivation), situational change, no benefit from therapy, stigma, conflict with others (family, care team) and feeling better.

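### Protocol 3.18 requires only related events to be recorded, which contradicts the AE definitions, the TSC's remit and the all-cause harms comparison, so complete capture by arm is not guaranteed

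*Combined protocol and SAP*

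**What the plan says.** **Recording rule (Protocol 3.18).** For AEs the rule names only those with a causal link "to the psychological therapy/assessment or qualitative interview that occur between baseline and end of study will be recorded in the participant medical notes"; the CRF is named as well. Occurrences that are not related come under "AEs that do not require reporting". The SAE paragraph covers SAEs related to therapy, assessment or an "interview occurring between baseline until end of study must be recorded on the SAE report form and emailed to Sponsor immediately". It then adds: "The SAE Report Form will be reviewed by the CI for assessment of causality".

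**Definitions (Protocol 3.17).** An AE is "Any untoward medical occurrence in a participant to whom psychological therapy/assessment or qualitative interview has been administered". The general SAE definition is likewise independent of cause and is extended by four named categories: suicide, suicide attempt, suicidal crisis without attempt, and severe symptom increase. Relatedness belongs to the separate reaction categories.

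**Oversight.** Under Protocol 3.6.1 the TSC "will review all instances of adverse events, regardless of whether they are judged to be attributable to the trial or interventions". Protocol 4.10.1 sends SAEs to the TSC with the attribution decision, whichever way it went, so that the TSC can review that decision. SHEAP 4.6 states: "The Chair of the TSC reviewed all serious adverse events".

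**Analysis.** SHEAP 5.3 defines the safety population as everyone randomised. SHEAP 7.6 summarises AEs and SAEs by arm and adds: "Treatment effects will be estimated by the difference in event rates and 95% CI for the differences". It does not restrict this to related events.

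**The concern.** A harms comparison between arms is interpretable only if an event has the same chance of entering the data in each arm. Under 3.18 an event must be recorded only once someone has judged it related, so a causal opinion decides whether it exists in the mandatory record.

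That opinion cannot work in the same way in both arms. In the iMAPS arm an event may be related to therapy, an assessment or an interview. In the usual-care arm there is no trial therapy, so only the last two routes exist.

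The oversight role is affected too. A TSC asked to check decisions of non-attribution needs to see the events concerned, yet under 3.18 a judgement of non-attribution is what removes the duty to complete a form. Anyone following 3.18 exactly could not be sure of meeting 3.6.1 or 4.10.1, or of supplying the data that SHEAP 7.6 expects.

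**Working it through.** **1. The rule against the rest of the plan.**

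| Place | Events covered |
| --- | --- |
| Protocol 3.17, definitions | AEs and SAEs whatever the cause |
| Protocol 3.18, recording and reporting | Related AEs and SAEs only |
| Protocol 3.6.1, TSC review | All AEs, attributable or not |
| Protocol 4.10.1, TSC review | SAEs, attributable or not |
| SHEAP 4.6, TSC Chair | All SAEs |
| SHEAP 5.3 and 7.6, analysis | AEs and SAEs in all randomised, no limit to related events |

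Only 3.18 applies the filter. The 4.10.1 and SHEAP 4.6 statements concern SAEs; 3.6.1 is the one that covers all AEs.

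**2. Circularity.** Under 3.18 the form is required if the SAE is related, and relatedness is assessed by the CI from the form. The second step presupposes forms for SAEs whose relatedness is still open, which the first step does not require.

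**3. Reproducing Supplementary Table 6.** Randomised: 31 iMAPS, 14 usual care.

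- Unrelated, iMAPS: SAEs 1 + 1 + 0 = 2; AEs 8; total 10.
- Unrelated, usual care: SAEs 0; AEs 3; total 3.
- Overall: 2 + 11 = 13, as the table states. Related events: 0 and 0.

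**4. The comparison with and without the filter.**

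- All tabulated events: 10/31 = 0.32 and 3/14 = 0.21 events per participant, a difference of 0.11.
- Related events only, as 3.18 requires: 0/31 and 0/14, a difference of 0. The exact 95% upper limits are 11.2% and 23.2%.

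None of the 13 events was one that 3.18 required anyone to record.

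**5. Precision of the all-event comparison.** Table 6 counts events, not people. *Assuming* each event is a different participant, the risk difference is 32.3% − 21.4% = +10.8 points (unrounded inputs), Newcombe 95% CI −18.7 to +33.2. If events cluster in fewer people, the point estimate could lie anywhere from 1/31 − 3/14 = −18 points to 10/31 − 1/14 = +25 points.

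**6. Sensitivity to incomplete capture (hypothetical).** Two further usual-care events left unrecorded would reverse the sign of the event-rate difference: 10/31 − 5/14 = 0.323 − 0.357 = −0.03. Two further iMAPS events would raise it to 12/31 − 3/14 = 0.387 − 0.214 = +0.17. The documents do not show that any event was missed; the figures show only how few would matter.

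**The case against.** The strongest reply is that practice was better than the text. Every event in Supplementary Table 6 is classed as unrelated and both arms contribute, so the literal filter did not produce the reported table. There are other routes to capture or review:

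- Protocol 3.17 has an adverse-event assessment completed at end of treatment and follow-up by assistants blind to allocation, with no relatedness filter stated.
- Suicidal crisis is defined from a Calgary Depression Scale item, and that scale is scheduled for everyone at all three assessments (Protocol 3.11).
- Hospital admissions and A&E attendances are collected through the service-use data (Protocol 3.11, SHEAP 7.7).
- Protocol 4.10.1 and SHEAP 4.6 describe TSC review of SAEs.
- The SAE paragraph of 3.18 itself treats relatedness as conditional once the form has arrived, which suggests loose drafting.

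This stands, and it rules out three stronger readings. A reader might infer that the reported comparison rests on a filtered subset and is biased; Table 6 does not support that. A reader might infer that the TSC could not see unrelated events; SHEAP 4.6 says its Chair reviewed all SAEs. A reader might infer that an unblinded person made the relatedness judgement; no section says who makes the first judgement under 3.18 or whether that person knew the allocation.

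It can also be said that harms are not a progression criterion and that no formal testing is planned. That limits the consequence but does not resolve the contradiction. The other routes do not replace AE and SAE recording: scheduled scales and service-use questionnaires depend on attendance, and nothing says their content is fed into the safety tables. Table 6 also shows no row for suicidal crisis without attempt or for severe symptom increase, both of which SHEAP 7.6 says will be tabulated. A reader cannot tell whether these were zero, not captured or placed elsewhere.

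**Conclusion.** The point holds as a contradiction in the plan with a real consequence for the harms analysis. Protocol 3.18, followed exactly, would give 0/31 v 0/14 where the trial tabulated 10 v 3 events. It is wrong as written, not merely short of detail.

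What follows is limited. Complete capture of unrelated events in each arm, and complete transfer of events to the TSC, is not guaranteed by the plan and cannot be verified from the documents. The by-arm comparison is therefore open to bias, of unknown direction and size. Nor is 10 v 3 evidence of an excess: on the assumption of one event per participant, the interval runs from −18.7 to +33.2 points.

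The 0 v 0 figure assumes that the relatedness classes in Table 6 are those that would have been applied when deciding whether to record each event.

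**What to change.** **Protocol 3.18, before the text is reused for a definitive trial.** Reconcile it with 3.6.1, 4.10.1 and SHEAP 7.6:

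- Require all SAEs, including the four added categories in 3.17, and the AE types that will be tabulated by arm, to be recorded in both arms over the same period regardless of relatedness.
- Send all SAEs to the CI, Sponsor and TSC.
- Assess relatedness and expectedness afterwards from the completed form, and let them govern expedited reporting only.

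**SHEAP 7.6.** State that the by-arm comparison is of all-cause events. List related events separately, and give counts of participants as well as events.

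**Report of this trial.** State how unrelated events were ascertained in each arm and which events the TSC received.

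**Cost.** Wording in two documents and a modest number of extra forms, with no new visits. The 13 events in 45 participants are only a rough guide to volume, since their completeness is the open question. Whether to log every unrelated non-serious occurrence is a proportionality choice for the sponsor; the firm case is for SAEs and for whatever AE types are compared between arms.
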